## Schedule of activities – without maintenance treatment

|                                             | 0              | 2 | 4 | 6 | 8 | 10 | 12             | 14             | 16             | 18             | 20               | 22 | 24             | 26 | 28             | 32             | 36             | 40             | 44             | 48             | 52               | 78             | 104            |
|---------------------------------------------|----------------|---|---|---|---|----|----------------|----------------|----------------|----------------|------------------|----|----------------|----|----------------|----------------|----------------|----------------|----------------|----------------|------------------|----------------|----------------|
| Full clinical assessment a       | X              |   |   |   |   |    | X              |                |                |                | X                |    |                |    |                | X              |                |                |                |                | X                |                |                |
| Telephone consultation                      |                |   |   |   |   |    |                | X b | X b | X b |                  |    | X c |    | X c |                | X c | X c | X c | X c |                  | X p | X p |
| Safety assessment d              |                |   |   |   |   |    |                | X              | X              | X              |                  |    |                |    |                |                |                |                |                |                |                  |                |                |
| Registration of adverse events e |                |   |   |   |   |    | X              | X              | X              | X              | X                | X  | X              | X  | X              | X              | X              | X              | X              | X              | X                |                |                |

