### Endpoints and statistical analyses

The primary outcome measures are safety and tolerability as measured by treatment-emergent adverse events.

The secondary objectives for efficacy are changes in outcome variables, from the baseline/run-in period (12 weeks) before intervention, and through 40 weeks follow-up from start of intervention for SF36 domains including SF36 Physical Function (SF36-PF) and SF36 Bodily pain (SF36-BP), DSQ-SF, Self-reported Function level, and Steps per 24 hours.

The pilot study is explorative, with no blinding or placebo group. We will not describe patients dichotomously as responders or non-responders. Rather, the outcome measures will be descriptive, and assessed by changes in the courses of variables from baseline through 52 weeks from inclusion, including a 12-week run-in before intervention, and 40 weeks after start of intervention. For patients receiving additional maintenance injections at weeks 26, 34 and 42, the analyses will be extended through follow-up to week 72. The outcome variables for efficacy will be assessed by General Linear Model (GLM) Repeated measures for time effects, with the baseline values given as mean values for the 12 week run-in period before start of intervention.

We will also perform analyses for changes in outcome measures at fixed time points compared to baseline, at end of run-in period (i.e. at 12 weeks) and again at 16, 18, 20, 22, 24, 28, 32, 40, 48 and 52 weeks, for patients receiving additional maintenance injections extended at four-week intervals to week 72. Differences in outcome measures from baseline, and from end of run-in at 12 weeks, to the fixed time points after intervention will be assessed by paired t-test or by Wilcoxon paired non-parametric tests.

Extended follow-up may be performed also after end of study, either by clinic attendance or by telephone, to monitor any toxicity or ongoing clinical responses.

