#### **Daratumumab dosing, injection, and injection-related reactions (IRR)**

Daratumumab subcutaneous injections will be given at a fixed dose of 1800 mg. A 15 ml syringe, which also contains recombinant hyaluronidase, is injected over 3-5 minutes into the abdomen approximately 7-8 cm to the right or left of the umbilicus (rotating injection sites for successive injections), on intact, healthy skin.

The patient will stay in the outpatient ward for at least 6 hours after the first Daratumumab injection, for observation of any injection-related reactions (IRR). Intravenous access will be established before the injection for administration of premedication and will be maintained throughout the observation period. Any allergic reactions or IRR will be treated according to standard hospital procedure.

If no IRR after the first injection, the observation period following the subsequent three injections will be 2 hours.

IRR after subcutaneous injections occurred in 9% of patients with multiple myeloma after the first injection, usually of grade 1-2. The risk of IRR will probably be lower in these patients without malignant plasma cells due to the low number of CD38 positive plasma cells. In the small patient series using daratumumab in autoimmune diseases, IRR was not reported to be a clinical problem.

If a patient suffers a severe allergic reaction or injection-related reaction (grade 4), the patient will not receive further daratumumab intervention.

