## Adverse events and Safety board

### Adverse events

Investigators will assess and classify adverse events (AE), serious adverse events (SAE), and SUSAR (suspected unexpected serious adverse reactions) according to the Common terminology criteria for adverse events (CTCAE), version 5.0 and the study drug SmPC.

For the purpose of safety and toxicity assessment, adverse events from grade 2 (moderate) and upwards, with possible, probable or certain causal relationship with the study drug will be reported. All SAE will be reported, regardless of causality.

Elective or pre-planned hospital admissions arranged prior to the start of study, or planned hospital admissions for trial specific procedures or treatment are not considered SAE.

Definitions and procedures for assessments and reporting of adverse events are described in appendix 1.

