### Safety aspects

The published case series using daratumumab in autoimmune diseases have reported good tolerability. The relatively high frequency of **infusion-related reactions (IRR)** seen in multiple myeloma, especially at first infusion, has not been observed as a clinical problem in the small published series of autoimmune conditions, possibly due to the low number of plasma cells in bone marrow and tissue niches compared to multiple myeloma patients who often carry a high tumor burden.

Moreover, aggravation of neutropenia and thrombocytopenia, which has been a concern during multiple myeloma treatment with daratumumab and concomitant chemotherapy, has not been reported in the case series of daratumumab monotherapy in autoimmune diseases.

**Hypogammaglobulinemia** from repeated anti-CD38 antibody intervention and plasma cell depletion may be a matter of concern, especially with long-term treatment. We do not anticipate that this will be a clinical problem when administering a mere four injections, but we will assess immunoglobulins regularly through follow-up, and also measure IgG subclasses at baseline and at the end of follow-up.

We will assess vaccination status with titers of antibodies to tetanus, diphtheria, pertussis and Covid-19, at baseline and repeated at end of follow-up (52 weeks).

Because daratumumab has not been used for ME/CFS, we will assess any occurrence of **anti-daratumumab antibodies (ADA)**, in plasma samples 2 weeks after the fourth injection (at week 20). Plasma samples will be screened for antibodies binding to daratumumab and the titer of any confirmed positive samples will be reported.

The efficacy and safety of the anti-CD38 antibody daratumumab in ME/CFS is unknown. We do not know whether the drug will be beneficial. In addition to high expression of plasmablasts and long-lived plasma cells, CD38 is also expressed on diverse subsets of B- and T-lymphocytes, including B-regulatory cells. Therefore, all biological and clinical effects may not be foreseen.

Although the tolerability in known autoimmune diseases, assessed from the small case series published so far, has been good, we do not know if there will be other side effects in ME/CFS. In theory, some patients could experience worsening of the disease. With this in mind, we will perform a safety review after treatment of the first two patients as described under "Intervention".

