#### Documenting assessment and reporting of adverse events

The investigator is responsible for ensuring that all AEs (including SAEs) that are observed or reported during the study, as outlined in the prior sections, are recorded on the eCRF. Adverse

events will be scored according to the NCI Common Terminology Criteria for Adverse Events, version 5.0 (See appendix VI). Investigator will assess the occurrence of AEs and SAEs at all subject evaluation time points during the study. All AEs and SAEs, whether volunteered by the subject, discovered by study staff during questioning, or detected through physical examination, laboratory testing, or other means, will be recorded in the subject's medical record and on the AE eCRF.

Each recorded AE or SAE will be described by its duration, severity, suspected relationship to the investigational product, and any action taken.

Adverse events will be reported from the time of signature of informed consent until the end of study for the patient.

If an AE or SAE is present at the withdrawal visit or at the subject's last participation in the study, it should be followed until the time of resolution or stabilized unless the subjects is lost to follow up. Resolution means the subject has returned to baseline state of health or the investigator does not expect any further improvement or worsening of the event.

Adverse events occurring after the end of follow-up in the study should also be reported if considered at least possibly related to the investigational medicinal product by the investigator.

Pre-existing conditions will be collected on the baseline concomitant diseases CRF, i.e., active (symptomatic) diseases of CTCAE grade 2, diseases under treatment, chronic diseases and long-term effects of past events as present at the time of baseline assessment.

All adverse events have to be reported with **the exception of:**

1. A pre-existing condition that does not increase in severity; the pre-existing condition should be reported on the baseline concomitant diseases CRF.
2. Any grade 1 adverse event.

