### Causality assessment of Serious Adverse Event

The investigator will decide whether the serious adverse events is related to the investigational treatment, i.e. daratumumab. The decision will be recorded on the serious adverse event report. The assessment of causality is made by the investigator using the following:

| RELATIONSHIP   | DESCRIPTION                                                                                                                                                                                                                                                                                                              |
|----------------|--------------------------------------------------------------------------------------------------------------------------------------------------------------------------------------------------------------------------------------------------------------------------------------------------------------------------|
| UNRELATED      | There is no evidence of any causal relationship                                                                                                                                                                                                                                                                          |
| UNLIKELY       | There is little evidence to suggest there is a causal relationship (e.g., the event did not occur within a reasonable time after administration of the trial medication).

There is another reasonable explanation for the event (e.g., the patient's clinical condition, other concomitant treatments).           |
| POSSIBLE       | There is some evidence to suggest a causal relationship (e.g., because the event occurs within a reasonable time after administration of the trial medication).

However, the influence of other factors may have contributed to the event (e.g., the patient's clinical condition, other concomitant treatments). |
| PROBABLE       | There is evidence to suggest a causal relationship and the influence of other factors is unlikely.                                                                                                                                                                                                                       |

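### The reporting rule for non-serious adverse events is narrower than the primary outcome and contradicts Appendix 1, so unblinded causality judgement decides what enters the primary safety result

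*Protocol*

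**What the plan says.** Under Endpoints and statistical analyses the protocol states: "The primary outcome measures are safety and tolerability as measured by treatment-emergent adverse events". No grade or causality limit is attached. Appendix 1, Definition of adverse events, defines an adverse event independently of any link to the drug and includes aggravation of a baseline condition.

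Under Adverse events, for safety and toxicity assessment, the rule is that "adverse events from grade 2 (moderate) and upwards, with possible, probable or certain causal relationship with the study drug will be reported". The next sentence has all serious events reported irrespective of cause, and the section refers to Appendix 1 for procedures.

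Other sections set different rules:

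- Data registration and management puts every event of CTCAE grade 2 or higher in the CRF, with no causality condition.
- Appendix 1, Documenting assessment and reporting of adverse events, says that all events, including those "detected through physical examination, laboratory testing, or other means, will be recorded" in the medical record and on the adverse-event eCRF. Suspected relationship to the drug is one of the attributes noted for each event. The same section requires all events to be reported with two exceptions: a pre-existing condition that has not worsened, and any grade 1 event.
- On timing, that section says: "Adverse events will be reported from the time of signature of informed consent until the end of study for the patient". In both schedules of activities the row "Registration of adverse events" is first ticked at week 12, and Evaluations also starts safety evaluation at week 12.

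The only causality scale stands in Appendix 1 under a heading for serious events. The trial has no blinding and no placebo group.

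**The concern.** The endpoint counts events that arise on treatment. The reporting rule counts, among non-serious events, those of at least grade 2 that the investigator links to the drug. The first quantity needs no judgement of cause. The second depends on it entirely, and here the person judging knows that every patient has received daratumumab and has no control patients for comparison.

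The protocol names one harm for which this matters most. Under Safety aspects it says: "In theory, some patients could experience worsening of the disease", and Possible risks repeats the point. Worsening of the disease under study is the event most easily put down to the disease itself. If it is non-serious and so attributed, the Adverse events rule leaves it out of the safety report.

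Safety and feasibility are the main purpose of the study, so the rule bears on its principal result. Two teams following different sections of this protocol could publish different adverse-event tables from the same patients.

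**Working it through.** The protocol states no sample size, power or error rate for this endpoint, so there is no planned figure to reproduce. The check is to take each class of event through each rule. I read treatment-emergent in its usual sense, as starting or worsening after the first injection; the protocol does not define it.

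**Step 1. Event classes against rules**

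| Class | Primary outcome | Adverse events (reporting) | Data registration (CRF) | Appendix 1, recording | Appendix 1, reporting |
|---|---|---|---|---|---|
| Serious, any cause | counts | reported | in, if grade 2 or above | recorded | reported |
| Non-serious, grade 2 or above, judged related | counts | reported | in | recorded | reported |
| Non-serious, grade 2 or above, judged unrelated, unlikely or not assessable | counts | **left out** | in | recorded | reported |
| Non-serious, grade 1 | counts | left out | **out** | **recorded** | excused |

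The third row is the main contradiction: two sections of the same protocol give opposite instructions for one event. The fourth row is a second one: Appendix 1 puts all events on the eCRF, while Data registration and management sets the CRF limit at grade 2 and Appendix 1 itself excuses grade 1 from reporting.

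**Step 2. The causality filter**

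The filter applies to non-serious events, but the only scale is headed for serious events, the one class exempt from the filter. The rule's top level is *certain*; the scale's is *definitely*. The scale also has *not assessable*, which the rule does not list, so such events drop out by default.

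**Step 3. A grade 2, non-serious worsening of ME/CFS**

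- It is an adverse event, because it aggravates the baseline condition.
- Appendix 1 requires it to be reported, since only unchanged pre-existing conditions are excused.
- Under Adverse events the outcome depends on the rating. The *unlikely* level includes the criterion "There is another reasonable explanation for the event", with the patient's clinical condition as an example; rated so, the event is left out. The *possible* level names the same factor as a contributor; rated so, it is reported.

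The same event can therefore fall on either side of the line at the investigator's discretion.

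**Step 4. Start of recording**

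Appendix 1 starts at consent. The schedule rows and Evaluations start at week 12. The footnote on the full clinical assessment includes an adverse-event assessment, and that assessment is ticked at weeks 0 and 12. Nothing specific to adverse events is scheduled at weeks 2 to 10.

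**Step 5. Scale**

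With n = 10, one patient is 1/10 = 10 percentage points of incidence. If that patient's only event is omitted, the result moves from 1/10 (exact 95% interval 0.3% to 44.5%) to 0/10 (upper limit 1 − 0.025^(1/10) = 30.8%). This shows the weight of one patient. It does not estimate how many events the rule would remove.

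**The case against.** The strongest reply is that the filter restricts reporting and not collection. Serious events are reported whatever the cause. Events of grade 2 or above enter the CRF whatever the cause, Appendix 1 records relationship as an attribute, and the Adverse events section itself defers to Appendix 1. The safety board monitors registered events. A reader might infer that the trial cannot report its own primary endpoint; the documents do not support that. All-cause events of grade 2 or above, and all serious events, can be tabulated from what is collected. Only an all-grade count is in doubt.

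Three further inferences also go too far.

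- *Worsening of ME/CFS will be lost.* It can be rated possible and so be reported. SF-36, DSQ-SF and Function level also follow it, independently of attribution. Those are efficacy measures, however, and do not put the event into the primary safety result.
- *The run-in yields no adverse-event data, a loss of 10 × 12 = 120 patient-weeks.* Appendix 1 starts recording at consent and an assessment falls at week 0, so the loss is not established. Treatment-emergent events exclude the run-in in any case, and its stated purpose is natural symptom variation. What stands is that the start times disagree.
- *Injection reactions show the size of the problem.* The protocol cites 9% after the first injection in myeloma, "usually of grade 1-2", which would give 0.09 × 10 = 0.9 patients. It also expects a lower risk here and gives no grade 1 share. Such reactions would ordinarily be judged related, so they do not illustrate the causality filter.

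A grade 2 threshold is a defensible choice. The objection does not remove the conflict in step 1: for non-serious events of grade 2 or above judged not related, the protocol gives two opposite instructions, and one of them departs from the primary outcome.

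**Conclusion.** The point holds as an inconsistency in how the primary outcome is reported. Followed as written, the Adverse events section would turn the non-serious part of the result from treatment-emergent events into investigator-attributed events of at least grade 2. In an open-label trial without a control group, that selection could make the safety result look more favourable.

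The affected class is non-serious events of grade 2 or above rated unrelated, unlikely or not assessable. Their number cannot be derived from the protocol. At that grade the all-cause result remains recoverable. The conflicts over grade 1 capture, the causality scale and the start of recording are secondary but belong to the same correction.

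The conclusion assumes that the Adverse events section could be taken to govern the published safety report. The protocol does not say which section prevails. It should be settled before the safety data are tabulated.

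**What to change.** 1. In Adverse events, delete the causality condition. State that all-cause treatment-emergent adverse events at or above one named minimum grade are reported as the primary outcome, with drug-related events shown as a subset.
2. Make Adverse events, Data registration and management, and the exception list in Appendix 1 agree on that grade. Bring the Appendix 1 statement that all events go on the eCRF into line with it.
3. Apply one causality scale to all adverse events, serious or not, use its terms throughout, and say how events that cannot be assessed are shown.
4. Reconcile the start of recording across both schedules of activities, Evaluations and Appendix 1.

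The cost is a wording amendment and a few more lines of tabulation for 10 patients. The sample size is unaffected. The downside is a slightly longer adverse-event table that may look less favourable. Removing the grade 2 threshold, adding run-in event rates or specifying exact intervals would be options for the sponsor; this correction does not need them.

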### Safety board/safety review

The safety aspect of the study will be monitored by [name], Haukeland University Hospital and [name], Dept. of Oncology, The Norwegian Radium Hospital, Oslo University Hospital. Members of the Safety board will be independent of the study investigators. They will monitor registered adverse events (AE) and serious adverse events (SAE), but will not perform clinical examinations of the patients.

The first safety review will be performed after the first two participants have completed all four daratumumab injections (at week 18-20), and before start of intervention for the remaining four patients. There will also be a safety review after all six patients have completed intervention.

